**Figure 2 figure2:**
[figure not shown]
Participant flow diagram.

### Statistical Analysis

Prior to analysis, interview audio recordings will be transcribed verbatim by 2 trained research assistants and verified by the primary researcher ([name]). Qualitative interview transcripts will be analyzed using the NVivo software package (version 12; QSR International), to assess in-depth feedback regarding MI-Coach: ED’s feasibility and acceptability. A thematic content analysis will be conducted to analyze the qualitative responses from the open-ended uMARS questionnaire and semistructured interview data using Braun and Clarke’s [36] framework. A bottom-up theoretical approach was used, in which the analysis was driven by the data generated through the semistructured interviews [36,53].

Additionally, quantitative analyses will be conducted using the R statistical package (version 4.2.0; R Core Team). Descriptive analyses of posttest feedback questionnaires, attrition data, and sessions completed will be used to determine the feasibility and acceptability of the MI-Coach: ED app. Means, SDs, ranges, and percentages will be calculated for all descriptive variables (ie, age, ethnicity, BMI, height, and weight), and total and mean scores will be calculated for app acceptability measures. Overall app use (ie, number of modules completed, days that the app was used, assessments and exercises completed, and logins) will be calculated using in-app data provided by Resiliens Inc.

Finally, tests of clinical significance [54] will be used to evaluate changes in clinical presentation across time points. The following categorizations will be used to identify whether change is clinically significant: reliably improved, in which there is reliable change and the clinical cutoff is no longer met; reliably deteriorated, in which there is a reliable change in the disordered direction and the individual’s score falls within the clinical range; and unchanged, in which neither criteria of the Jacobson-Truax method are met [54,55]. Finally, exploratory growth curve analyses will be used to model individual participants’ change trajectories across the 4-week pilot test period [56].

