**Methods:**

Phase I adapted the content and interface of an existing app based on evidence-based principles (MI-Coach) for an ED population. Phase II pilot tested the app through a pre-post evaluation. Participants (n=30) aged 18 years and older were recruited from ED treatment waitlists in British Columbia, Canada. After completing baseline assessments evaluating demographic and clinical variables (eg, motivation, eating pathology, depression, and anxiety symptoms), participants were provided access to MI-Coach: ED for 1 month. Participants completed postintervention assessments and provided both quantitative and qualitative feedback on the app. Feasibility will be evaluated through the total number of participants recruited, study dropout rates, and engagement indicators (eg, modules completed) within the app. Acceptability will be assessed through self-report measures and semistructured exit interviews, which will explore user experiences, perceived benefits, and barriers to app engagement. Additionally, exploratory analyses will examine changes in motivation and ED symptoms before and after the intervention.

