### Study Population

#### Sample Size Estimation

Given the focus of this study on the acceptability and feasibility, rather than the efficacy, of the MI-Coach: ED app, formal analytic methods were not used to estimate the prehoc sample size. In keeping with previous feasibility studies in the ED field [14,33,34] and pilot study guidelines, which suggest that modest sample sizes based on the pragmatics of recruitment are sufficient when evaluating the processes, feasibility, and preliminary acceptability of novel interventions [32,35], a sample size of 30 participants was selected, recruited while they wait for ED services and treatments in British Columbia, Canada. Additionally, it was determined that qualitative interviews would be conducted with interested participants on a rolling basis until thematic saturation is reached [36].

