### Outcomes and Measures

The primary outcomes that will be evaluated are the overall acceptability and feasibility of the MI-Coach: ED (Multimedia Appendix 3)*.* Feasibility will be assessed through attrition rates throughout the study period, frequency of app use, and module completion. Acceptability will be assessed through qualitative and quantitative feedback from participants through semistructured interviews and self-reports. Additionally, exploratory analyses will be conducted regarding the impacts of the MI-Coach: ED app on motivation and associated clinical characteristics.

Self-reported demographic data, including gender identity, age, level of education, ethnicity, and socioeconomic status were collected using Qualtrics, a web-based and secure data collection platform. Additionally, clinical data (ie, weight and height, history of ED treatment, age of ED onset, presence of cognitive difficulties, sensory deficits, history of traumatic brain injury, other mental health comorbidities, and ED waitlist experiences) was collected. The Sick, Control, One, Fat, and Food questionnaire [43], a brief screener that identifies the presence of common ED symptoms, was used to determine eligibility prior to enrollment. Clinical characteristics (ie, eating pathology, recovery motivation, body dissatisfaction, depression, and anxiety symptoms) were evaluated through several self-report questionnaires administered at baseline and posttest, including the Eating Disorder Examination Questionnaire (EDE-Q) [44], the Readiness and Motivation for Change Questionnaire (RMQ) [45], the Body Shape Questionnaire (BSQ) [46], the Patient Health Questionnaire-9 (PHQ-9) [47], and the 7-item General Anxiety Disorder Scale (GAD-7) [48]. Additionally, technological literacy was evaluated at baseline using the Mobile Device Proficiency Questionnaire [49] and the eHealth Literacy Scale [50].

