## Discussion

### Anticipated Results

This study aimed to evaluate the feasibility and acceptability of MI-Coach: ED, an app designed to support motivation for ED recovery among individuals on treatment waitlists. It is anticipated that the intervention will be feasible to implement, with a high rate of participant engagement with the app, and that MI-Coach: ED would be perceived as an acceptable and useful tool for supporting motivation during the waitlist period. Prior research suggests that digital mental health interventions targeting ED populations are generally acceptable and feasible to users, particularly when they incorporate evidence-based therapeutic principles such as MI [15,28]. Additionally, app-based self-help interventions have demonstrated high engagement rates, which MI-Coach: ED was designed to include [23,27]. Furthermore, we anticipate that exploratory analyses will demonstrate preliminary improvements in motivation and ED-related symptoms following app use, given findings that brief MI-based interventions can enhance motivation for change, improve treatment engagement, and reduce ambivalence in ED populations [8,14,16,17]. As motivation is a key predictor of ED treatment outcomes [11], even small gains during the waitlist period could have meaningful clinical implications.

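### Feasibility and acceptability are to be determined from point summaries of at most 30 people, with no interval or benchmark in the visible text; they should be estimated with 95% confidence intervals.

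*Protocol article*

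**What the plan says.** Outcomes and Measures names the primary outcomes: "The primary outcomes that will be evaluated are the overall acceptability and feasibility of the MI-Coach: ED". On feasibility it says: "Feasibility will be assessed through attrition rates throughout the study period, frequency of app use, and module completion". The Methods paragraph of the Abstract lists the indicators slightly differently and adds recruitment: "Feasibility will be evaluated through the total number of participants recruited, study dropout rates, and engagement indicators". Acceptability is to come from interviews and from self-report, including the adapted Technology Acceptance Model questionnaire (TAM-Q) and the uMARS.

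Statistical Analysis then states how the quantitative material leads to a conclusion: "Descriptive analyses of posttest feedback questionnaires, attrition data, and sessions completed will be used to determine the feasibility and acceptability". For the acceptability scales it plans total and mean scores. For app use it plans counts such as modules completed, days of use, exercises and logins. The same section also plans a thematic analysis of the interviews and the open-ended uMARS answers.

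On size, Sample Size Estimation says "a sample size of 30 participants was selected" and explains that "formal analytic methods were not used to estimate the prehoc sample size". No section in the visible text gives a target, benchmark or interval for recruitment, attrition, app use, TAM-Q or uMARS.

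**The concern.** To determine feasibility is to reach a conclusion about it. The text names the material for that conclusion, but not how precise the material is or what value it would be compared with. A retention percentage or mean rating from 30 or fewer people is compatible with a wide range of true values, and the summaries named do not show that range.

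The figures will be used. The Discussion says that recruitment, retention and engagement data will shape the app and the recruitment methods for later large-scale evaluations. A bare percentage carried forward in that way is easily taken as a planning value. Data analysis was already under way when the article was written, so a benchmark chosen now could be influenced by the results.

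The same section sets explicit categories for the exploratory clinical outcomes (reliably improved, reliably deteriorated, unchanged). It gives nothing comparable for the primary ones.

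**Working it through.** **Inputs.** The sample size of 30 comes from Sample Size Estimation. It was chosen on pragmatic grounds, with no error rate, expected proportion or precision target, so there is no planned figure to reproduce. The article gives no observed counts and no posttest numbers. The counts below, and the posttest numbers of 24 and 20, are assumptions chosen to show the range.

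**Proportions (retention, any app use, module completion).** The exact (Clopper-Pearson) 95% limits for x out of n are:
- lower limit = 2.5% quantile of Beta(x, n − x + 1)
- upper limit = 97.5% quantile of Beta(x + 1, n − x)

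For 21/30, the lower limit comes from Beta(21, 10) and is 0.506. The upper limit comes from Beta(22, 9) and is 0.853. The same formula gives:

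| Observed | Percent | Exact 95% CI |
|---|---|---|
| 15/30 | 50% | 31% to 69% |
| 18/30 | 60% | 41% to 77% |
| 21/30 | 70% | 51% to 85% |
| 24/30 | 80% | 61% to 92% |
| 27/30 | 90% | 73% to 98% |
| 16/20 | 80% | 56% to 94% |

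At n=30 the full width runs from 0.979 − 0.735 = 0.244 (about 24 percentage points) at 27/30 to 0.687 − 0.313 = 0.374 (about 37 points) at 15/30. Wilson intervals are somewhat narrower (52% to 83% for 21/30) and lead to the same reading.

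**Means (TAM-Q, uMARS).** The 95% half-width in SD units is t(0.975, n − 1)/√n:
- n=30: 0.373
- n=24: 0.422
- n=20: 0.468

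**What a benchmark chosen late could do.** Suppose, purely for illustration, that a true retention of 60% is unacceptable and 80% is good. The exact binomial chance of passing is then:

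| Rule | True rate 60% | True rate 80% |
|---|---|---|
| at least 21/30 | 17.6% | 93.9% |
| at least 23/30 | 4.4% | 76.1% |

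Moving the cutoff by two people changes the false-pass risk about fourfold (17.6/4.4 = 4.0). If the same 60% were judged on the exact lower limit, at least 24/30 would be needed: 23/30 has a lower limit of 57.7% and 24/30 one of 61.4%.

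**The case against.** The strongest reply is that this is a condensed article about a formative pilot. Interval methods are commonly left to an analysis plan, descriptive analyses do not exclude intervals, and a reader can compute an exact interval from any reported x/30. Multimedia Appendix 3 is cited in the very sentence that names the primary outcomes; it is not shown and could hold benchmarks. Much of this stands. A missing interval alone would be no finding. What remains is that the article states a method, point descriptives that determine the outcome, and that method as written gives neither a yardstick nor a measure of precision.

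Several stronger readings are tempting, but the documents do not support them.

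- A reader might infer that almost any result could be called feasible, or that the conclusion cannot fail. That goes too far. The thematic analysis also addresses feasibility and acceptability and could yield a negative conclusion, and the unseen appendix may contain criteria.
- A reader might take "Means, SDs, ranges, and percentages will be calculated for all descriptive variables" as the summary plan for the primary outcomes. The parenthesis that follows lists age, ethnicity, BMI, height and weight, so it describes the sample.
- A reader might treat the anticipated result, "with a high rate of participant engagement with the app", as the standard to be met. It stands in the Discussion as an expectation and is not a decision rule.
- A reader might assume a formal go/no-go decision. None is stated. Study Design speaks of initial feasibility and acceptability and of finding problems with design and delivery; the Abstract calls such work a first step before efficacy trials.
- A reader might conclude that 30 is too few. A pragmatic sample without a power calculation is acceptable for a pilot and is not criticised here.

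**Conclusion.** The concern holds in a limited form. As written, the quantitative part of the primary conclusion rests on point values from at most 30 people, with no interval and no benchmark in the visible text. At n=30 an observed proportion between 50% and 90% carries an exact 95% interval about 24 to 37 percentage points wide. A mean score is known to within 0.37 SD at n=30, or 0.47 SD if 20 people respond.

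The observed counts, the posttest numbers and the 60% and 80% rates are illustrative assumptions. The absence of a benchmark is established only for the visible text, and the qualitative strand is outside this calculation. The point concerns how the results are worded and reported; it does not challenge the design or the data collected.

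**What to change.** In Statistical Analysis:

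1. Replace the verb determine with estimate in the sentence on the descriptive analyses.
2. Report retention to posttest, any use of the app, and completion of each of the seven modules with exact 95% confidence intervals, stating the denominator each time.
3. Report TAM-Q and uMARS means with t-based 95% confidence intervals and the number of respondents.
4. Draw no quantitative conclusion that the app is feasible or acceptable unless a benchmark was fixed before the data were seen. If Multimedia Appendix 3 or another dated document holds one, cite it. Label any benchmark added now as set after data collection, and judge it on the interval. Dating it does not make it prespecified.

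The thematic analysis can stay as planned. The cost is a few lines of text and code, with no new data. The one downside is that the results will look less certain.

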**Objective:**

This multiphasic mixed methods study aims to develop and assess the feasibility and acceptability of MI-Coach: ED, a novel app designed to increase motivation among women waitlisted for ED treatment. Specifically, this study seeks to determine participant engagement levels, user satisfaction, and perceived usability of the app, as well as to explore preliminary trends in motivation and ED-related symptoms following app use.

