The subsequent pilot-test portion of the study consisted of a four-week period during which participants used the app in a naturalistic way. Following study completion, participants were compensated CAD $10 (≈US $7.10) for each study portion completed (ie, baseline questionnaire package, onboarding session, posttest questionnaire package, and exit interview), receiving up to CAD $40 (≈US $28.41) through the Tango Card rewards platform. To reduce the impact of possible confounds (eg, financial motivation), participants were informed that their compensation would not be impacted by their app use during the pilot test phase and that there are no minimum requirements for app use. Once the pilot test was completed, a second brief consent form (Multimedia Appendix 5) and posttest questionnaires assessing self-reported clinical features (ie, the EDE-Q, RMQ, PHQ-9, GAD-7, and BSQ) and feedback regarding the app (ie, the adapted TAM-Q and uMARS) were completed. Finally, participants were invited to participate in a videoconferencing-based exit interview to provide additional feedback on their experience with the study author. The semistructured interview guide (Multimedia Appendix 6) was used as an outline to standardize the interview process across participants [52].

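### Change on the five clinical scales is judged by an improved/deteriorated tally that cannot give the mean change or effect size the article wants, and the tally's categories leave gaps

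*Protocol article*

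**What the plan says.** The Outcomes and Measures section of the protocol article makes acceptability and feasibility primary and treats clinical change as exploratory. Eating pathology, recovery motivation, body dissatisfaction, depression and anxiety are measured with the EDE-Q, RMQ, BSQ, PHQ-9 and GAD-7, described as "several self-report questionnaires administered at baseline and posttest". Each scale is therefore scored twice.

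For these scales the Statistical Analysis section says "tests of clinical significance [54] will be used to evaluate changes in clinical presentation across time points". Participants are sorted into three groups:

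- **Improved:** "reliably improved, in which there is reliable change and the clinical cutoff is no longer met".
- **Deteriorated:** a reliable worsening with a score in the clinical range.
- **Unchanged:** neither criterion is met.

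The section then adds exploratory growth curves of individual trajectories over the four weeks, without naming the outcomes they cover. The means and SDs it lists are for demographic and body-size variables, with totals and means for the acceptability measures. The five clinical scales are not in that list.

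The aims are worded as average change. The Objective is to "explore preliminary trends in motivation and ED-related symptoms following app use", and the Hypotheses section expects motivation to improve. Anticipated Results remarks that "even small gains during the waitlist period could have meaningful clinical implications". The Conclusions section wants effect size estimates from these analyses to guide the power calculation of a later randomised trial. On size, "a sample size of 30 participants was selected" and "formal analytic methods were not used to estimate the prehoc sample size".

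**The concern.** The aims concern how far scores move on average and how large that movement is. The one analysis named for evaluating clinical change counts how many participants pass a double hurdle instead: a change beyond measurement error and a crossing of the clinical cutoff. A group can shift by an amount the article would regard as potentially meaningful while few of its members pass both hurdles.

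Two things are at stake. A reader of the tally could take a modest improvement in motivation for no sign of improvement. And the later trial would lack the mean change and the SD of change it is meant to take from this pilot. The category definitions also leave some participants without a place, so two analysts could produce different tallies from the same data.

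**Working it through.** The article gives no effect size, SD, reliability or cutoff, so there is no stated figure to reproduce. The only numerical input from the document is n = 30, with two time points. Everything else in steps 1 to 3 is an assumption, shown as a range: reliability 0.8 to 0.9; pre-post correlation 0.6 to 0.75; mean gain 0.2 to 0.5 baseline SD; cutoff 0.5 to 1.0 SD on the healthy side of the baseline mean (31% to 16% already below it under normality); normally distributed scores with equal SD at both times.

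**1. Reliable-change threshold, in baseline SDs: 1.96 × √(2(1 − reliability)).**

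- Reliability 0.8: 1.96 × √0.4 = 1.24.
- Reliability 0.9: 1.96 × √0.2 = 0.88.

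Both are well above an average gain of 0.2 to 0.5 SD.

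**2. Share of participants in each category, by simulation over the grid above.** Improved means a gain beyond the threshold with the cutoff crossed. Deteriorated means a loss beyond the threshold with the posttest score in the clinical range.

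| True mean gain | Improved | Neither improved nor deteriorated |
|---|---|---|
| 0.2 to 0.3 SD | 3 to 14% (about 1 to 4 of 30) | 78 to 95% |
| 0.5 SD | 7 to 19% | 76 to 92% |

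The group in the last column is not all unchanged as the article words it. At gains of 0.2 to 0.5 SD, 3 to 19% of all participants have a reliable gain without crossing the cutoff, and 4 to 15% cross it without a reliable change.

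**3. What the continuous scores give with the same 30 participants.** The SD of the change is √(2(1 − correlation)): √0.8 = 0.894 at correlation 0.6 and √0.5 = 0.707 at 0.75. The 95% half-width is t × SD/√n with t = 2.045 on 29 degrees of freedom: 2.045 × 0.894/√30 = 0.33 SD and 2.045 × 0.707/√30 = 0.26 SD.

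As an illustrative yardstick only, since the article plans neither test, two-sided 5% power would be:

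| True mean gain | Paired mean change | Improved versus deteriorated, exact sign test |
|---|---|---|
| 0.2 SD | 22 to 32% | 0 to 1% |
| 0.3 SD | 43 to 61% | 0 to 4% |
| 0.5 SD | 84 to 96% | 1 to 20% |

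**4. Growth curves on two occasions.** A linear model with individual intercepts and slopes needs four variance parameters: intercept variance, slope variance, their covariance and residual variance. Two occasions supply three second moments: two variances and one covariance. Since 4 > 3, individual slopes cannot be separated from residual error, and curvature cannot be fitted. What remains is the average effect of time, which with complete pairs is the pre-post mean change.

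**5. The category rules, with no assumptions.**

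- The improved category needs both criteria and the unchanged category needs neither. A participant who meets exactly one on the improving side belongs nowhere. Likewise, a reliable worsening that ends outside the clinical range fits no category.
- A cutoff can only be no longer met by someone who met it at baseline. The Eligibility Criteria admit subthreshold eating disorders and set no depression or anxiety threshold, so some participants may start below a cutoff. They can never count as improved on that scale, and the article does not take them out of the denominator.

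**The case against.** The strongest reply is that the plan does not discard the continuous scores. The growth curves use them, their time effect is the mean change, and the stated wish for effect sizes shows an intention to quantify change. The classification is an established method for describing individuals, not a hypothesis test. The sample was chosen for feasibility, so power is a poor yardstick. A condensed article may also leave summary statistics to a fuller document.

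Much of this stands. A reader might infer any of the following, and the document does not support them:

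- **That the plan as a whole throws away most of the information.** This describes the tally alone, and its size depends on the assumed reliability, correlation and cutoff.
- **That the article expects small average gains.** It anticipates improvements of unstated size and separately says small ones could matter.
- **That everyone not improved or deteriorated is counted as unchanged.** Those meeting one criterion are not.
- **That a weak test of improved against deteriorated is planned.** None is.

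The reply does not reach the remaining point. On these scales the curves cannot do what they are named for, which is to describe individual trajectories. Nor does the article say that these scales are their outcome. The mean change would be a by-product of a model that two occasions cannot support. The gaps in the categories are in the rules the article states, so they are not a matter of omitted detail.

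**Conclusion.** The point holds for exploratory analyses in a feasibility pilot, so its consequence is limited to the motivation hypothesis, the description of symptom trends and the effect size carried into the later trial. The primary outcomes are untouched.

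The tally cannot yield a mean change or an effect size; that needs no assumption. The gaps in the categories and the problem of participants below a cutoff at baseline follow from the wording alone, although how many participants they affect is unknown. That roughly 75 to 95% would be neither improved nor deteriorated at mean gains of 0.2 to 0.5 SD rests on the assumed ranges and on one normal model applied to five different scales. It shows the order of size and is not a forecast. The change is worth making because it is cheap and supplies what the article says it wants.

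**What to change.** In Statistical Analysis:

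1. For each of the EDE-Q, RMQ, BSQ, PHQ-9 and GAD-7, report the mean paired change (posttest minus baseline) with its SD and 95% confidence interval as the main exploratory estimate. Describe it as pre-post change, without attributing it to the app, since there is no comparison group. Let this replace individual growth curves on two points.
2. Keep the Jacobson-Truax classification as a secondary, individual-level description. Make it exhaustive: add a category for reliable change without crossing the cutoff, and state where those who cross without reliable change are placed.
3. Calculate the proportion whose cutoff is no longer met only among participants in the clinical range on that scale at baseline, and show that denominator.

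The cost is a few sentences and one extra table from data already collected; the Results section says analysis was still under way. The drawback is that the denominators of the secondary proportions will differ from scale to scale.

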#### Eligibility Criteria

Eligibility criteria were (1) being on a waitlist to receive services for an ED-specific concern and not for a separate mental disorder in British Columbia, (2) being at least 18 years of age, (3) self-identifying as a woman, (4) fluency in written and spoken English, (5) meeting the criteria for a diagnosis of a threshold or subthreshold ED (ie, BN, AN-R, AN-BP, BED, and OSFED), (6) absence of psychosis or diagnosis of a schizophrenia-spectrum disorder, and (7) absence of cognitive impairments or sensory deficits that may interfere with technology use (eg, hearing impairments and recent traumatic brain injury).

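### The three clinical-change categories never count a reliable improver who stays in the clinical range as improved, while an equal reliable worsening there counts as deterioration

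*Protocol article*

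**What the plan says.** The Statistical Analysis section of the protocol article says that "tests of clinical significance [54] will be used to evaluate changes in clinical presentation across time points" and then defines three categories after Jacobson and Truax:

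- The first, for benefit, is "reliably improved, in which there is reliable change and the clinical cutoff is no longer met".
- The second, for harm, is "reliably deteriorated, in which there is a reliable change in the disordered direction", provided also that the participant's "score falls within the clinical range".
- The third, for no change, is "unchanged, in which neither criteria of the Jacobson-Truax method are met".

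No other text in the article deals with this classification. It gives no cutoff, reliability or reliable-change threshold for any scale. The Outcomes and Measures section lists the scales given at baseline and again among the "posttest questionnaires assessing self-reported clinical features (ie, the EDE-Q, RMQ, PHQ-9, GAD-7, and BSQ"). It does not say which of them will be classified. The Eligibility Criteria require that participants be on an ED waitlist and be "meeting the criteria for a diagnosis of a threshold or subthreshold ED". Outcomes and Measures makes feasibility and acceptability primary and calls the analyses of motivation and clinical characteristics exploratory.

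**The concern.** The improvement and deterioration rules do not treat equal changes equally. 'Improved' requires a reliable change and leaving the clinical range. 'Deteriorated' requires a reliable change and being in the clinical range, which is where women waiting for ED treatment can mostly be expected to start. Partial but reliable improvement, a plausible result of four weeks with a motivational app, gets no credit, while worsening of the same size does.

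This is a fault in a stated rule, not detail left to a fuller plan: the three definitions are given as the ones to be used. Under Anticipated Results, the article argues that even small gains during the wait could matter clinically, and under Conclusions it intends the exploratory findings to guide a full-scale trial. With 30 participants, a few people placed in the wrong row change how the tally reads.

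**Working it through.** **No figure to reproduce.** The article gives no category counts or thresholds. The first two steps use only its definitions; the last two need assumed inputs, marked as such.

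**1. Enumeration.** Start range (2) × end range (2) × reliable direction (3) gives 12 cells. Two are impossible: worsening while leaving the clinical range, and improving while entering it. The strict wording treats the other 10 as follows.

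| Start → end | Reliable improvement | No reliable change | Reliable worsening |
|---|---|---|---|
| Clinical → clinical | **no category** | unchanged | deteriorated |
| Clinical → non-clinical | improved | no category | impossible |
| Non-clinical → clinical | impossible | no category | deteriorated |
| Non-clinical → non-clinical | no category | unchanged | no category |

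Five of the 10 feasible cells have no category. The first row shows the asymmetry: equal and opposite reliable changes by women who start and end in the clinical range are handled differently.

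**2. Direction when nothing changes on average.** Let baseline and posttest be exchangeable.

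- P(deteriorated) = P(worsens reliably, starts clinical) + P(worsens reliably, starts non-clinical, ends clinical). Someone who starts clinical and worsens necessarily ends clinical.
- P(improved) = P(improves reliably, starts clinical, ends non-clinical). By exchangeability this equals the second term above.
- The difference is P(worsens reliably, starts clinical) ≥ 0.

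The shortfall of 'improved' therefore needs no assumed reliability or cutoff, only the reading that 'no longer met' means crossing the cutoff.

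**3. Size under assumed inputs.** Assume bivariate normal scores with SD 1, reliability 0.85, pre-post correlation ρ of 0.5 or 0.7, and a cutoff 0.5, 1.0 or 1.5 SD below the baseline mean (about 69% to 93% clinical at baseline). The reliable-change threshold is 1.96 × √(2 × (1 − 0.85)) = 1.07 SD. The SD of change is √(2(1 − ρ)), that is 1.00 or 0.77.

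*Zero mean change.* Reliable change in each direction is 1 − Φ(1.07/1.00) ≈ 14.2% or 1 − Φ(1.07/0.77) ≈ 8.3%. Across the scenarios 1.6% to 7.8% are labelled improved and 7.5% to 14.1% deteriorated. Within each ρ:

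| ρ | True reliable worsening | Labelled deteriorated |
|---|---|---|
| 0.5 | 14.2% | 13.1% to 14.1% |
| 0.7 | 8.3% | 7.5% to 8.2% |

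The deterioration count is thus at or slightly below the truth. The imbalance comes from missing improvers.

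*True mean improvement 0.4 SD.*

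| ρ | Reliable improvers | Labelled improved (cutoff 0.5 / 1.0 / 1.5 SD below mean) | Share not labelled |
|---|---|---|---|
| 0.5 | 25.0% | 15.5 / 12.0 / 7.3% | 38 / 52 / 71% |
| 0.7 | 19.2% | 10.6 / 8.2 / 5.1% | 45 / 57 / 73% |

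The last column is 1 − labelled/reliable, for example 1 − 15.5/25.0 = 38%. In people, the unlabelled number between 30 × (19.2% − 10.6%) = 2.6 and 30 × (25.0% − 7.3%) = 5.3 of 30, before attrition.

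**4. Second model, and who the unlabelled are.** Assume an SD of true change of 0.5, a mean improvement of 0.5 SD and 93% clinical at baseline. Per 30 participants:

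| Reliability | Reliable improvers | Labelled improved | Improved but still clinical | Reliable worseners counted |
|---|---|---|---|---|
| 0.8 | 5.4 | 2.1 | 3.1 | 0.46 of 0.46 |
| 0.9 | 8.6 | 2.7 | 5.6 | 0.59 of 0.60 |

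The remaining improvers (about 0.2 and 0.4) started below the cutoff. That second group grows as fewer start clinical: at 69% clinical and reliability 0.8, 1.1 stay clinical and 1.0 started below. The unlabelled share in step 3 likewise contains both groups.

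**The case against.** **'Unchanged' may be a catch-all.** If 'neither criteria' means neither of the two categories just described, all five empty cells become 'unchanged' and the table sums to the sample. This reading is possible, so one cannot assert that the table will fail to add up. It does not cure the fault: a reliable improver is then reported as unchanged.

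**The two rules may be mirror images.** If 'no longer met' means only that the posttest score is below the cutoff, both rules become reliable change plus end state. The words 'no longer' speak against this, but it cannot be excluded. The tilt then depends on case mix. With no net change and reliability 0.8 in the second model, it is 0.6 improved against 1.8 deteriorated per 30 at 93% clinical, nil at 50%, and reversed at 31% (1.8 against 1.4). The article gives no baseline distribution, and PHQ-9 and GAD-7 scores are not entry criteria, so the balance could differ by scale. Even so, the reliable improver who stays in the clinical range is still not counted as improved.

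**Stronger readings a reader might infer.**

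- *That the scheme produces a false excess of deterioration, so that an ineffective app would look harmful.* Step 3 shows otherwise: labelled deterioration does not exceed true reliable worsening. With real benefit, 'improved' can still exceed 'deteriorated' (2.1 against 0.46 per 30 in step 4).
- *That subthreshold participants can never be classed as improved.* Subthreshold ED is a diagnostic status, not a score below a questionnaire cutoff, and no cutoff is stated.
- *That the scheme cannot be applied to the RMQ.* The article describes neither the RMQ's scoring nor its norms and does not say which scales will be classified. This supports a request for clarification, no more.

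**The analysis is exploratory.** The primary outcomes lie elsewhere and no decision or progression rule hangs on these categories. That stands, and it limits severity.

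**Conclusion.** The point holds under every reading of the definitions: a reliable improver who remains in the clinical range is not counted as improved, and an equal reliable worsener in that range is counted as deteriorated. Where most participants start in the clinical range, which is expected on eating pathology but not documented, improvement is undercounted relative to deterioration.

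The size cannot be fixed from the article. Roughly 40% to 70% of reliable improvers unlabelled is an illustration that rests on the assumed reliability, correlation, cutoffs and mean change of step 3 and on the crossing reading. The enumeration and the algebra do not need those values. This should be fixed, but it is not critical, since it affects a secondary, exploratory description in a sample of 30.

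**What to change.** For each scale that has a clinical cutoff, use four categories that cover every case:

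- **Recovered:** reliable improvement and crossing out of the clinical range, with the number in the clinical range at baseline printed as the denominator.
- **Improved:** reliable improvement without crossing.
- **Unchanged:** no reliable change.
- **Deteriorated:** reliable worsening.

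For any scale without a clinical cutoff, report reliable change by direction only. State which scales are classified, and the cutoff and reliability used for each.

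Counting all reliable change by direction removes the tilt. In the second model with no net change, improved and deteriorated become 1.9 against 1.9 per 30 at reliability 0.8, and 2.9 against 2.9 at 0.9.

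Recruitment has ended and analysis is underway, so report the three published categories alongside, state how 'unchanged' and 'no longer met' were read, and label the four-category table as supplementary. The cost is a few sentences and one or two extra table rows; no new data are needed.
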